### Therapists

Therapists are recruited from courses in advanced clinical training for behavioral therapy and are randomly allocated to one of the two conditions. The randomization to either CT plus enhanced BEs or standard CT is uniquely conducted to prevent contamination.

In each condition, training comprises three 8-h days:

In the CT plus enhanced BEs condition, training will focus on the specific competencies to derive, plan, conduct, and analyze BEs.

In the standard CT condition, training will focus on the specific competencies to practice techniques of cognitive restructuring.

### Adherence Checks

Adherence refers to (a) the use of prescribed and avoidance of proscribed interventions by the manual, and (b) the extent to which the interventions are conducted in line with the manual. Thus, adherence will be measured in two ways:
After each session, therapists will report which interventions they administered using a checklist of interventions.In addition, three randomly selected videotapes of each treatment (one from stage 1 and two from stage 2) will be rated on the Cognitive Therapy Adherence Scale (CTAS) [18]. Videotapes will be rated by qualified assessors who have been trained in previous projects and are experienced in the assessment of adherence to SAD-specific CT.

### Randomization

We will use two levels of randomization. Firstly, therapists are randomized to either CT + BEs or Standard CT as described above. Secondly, participants will be randomly assigned to a therapist of one of the two treatment conditions. The random allocation sequence will be generated by a randomization program [19]. Allocation to treatment of the patients is concealed from investigators and patients. The random allocation schedule will be drawn up and administered by a psychologist from another department of the university who is not involved in the further study process. After meeting the inclusion criteria, the participant is allocated by this psychologist to a therapist of one of the treatment conditions. The investigators and therapists are informed about the allocation.

### Ethical Issues

A protocol of the proposed project, informed consent document, and any other appropriate documents have been submitted to the independent Ethics Committee of Goethe University Frankfurt. Before the first subject is enrolled in the treatment study, all ethical and legal requirements have been met. The investigator will keep a record of all communications with the Ethics Committee and the regulatory authorities.

Before being admitted to the treatment study, the subject must consent to participate after the nature, scope, and possible consequences of the study have been explained in a form understandable to him or her. The subject must give written consent. A copy of the signed informed consent document will be given to the subject. The documents will be in a language understandable to the subject and will specify who informed the subject.

During the study, subjects will be identified solely by means of their initials, date of birth, and individual identification code (subject number, randomization number). Study findings stored on a computer will be stored in accordance with local data protection laws and will be handled in the strictest of confidence. Investigators will maintain a personal subject identification list (subject numbers with the corresponding subject names) to enable records to be identified.

Participating patients are provided with a treatment according to good clinical practice, i.e., CT according to the treatment guidelines of the German Psychological Association [20]. The cognitive interventions have no known risk, and no psychotherapy study for cognitive interventions in other psychiatric disorders has yet reported any adverse side effects. Suicidal tendencies will be checked regularly. If action is necessary, an outpatient service is available and admission to cooperating clinics is possible. The Center of psychotherapy, Goethe University Frankfurt will compensate to those who suffer harm from trial participation.

### Outcome Measures

The primary outcome measure is treatment response between baseline and posttreatment as assessed by the improvement item of the Clinical Global Impression Scale (CGI) modified for individuals with social anxiety disorder [21]. The CGI is a standard primary outcome measure in psychopharmacologic studies and has two components. The CGI-Severity (CGI-S) contains a Severity of Illness item that provides information about the current severity of social phobic symptoms. The severity rating is made by a clinician on a seven-step categorical scale with 1 representing “normal” or “not at all ill” and 7 representing “among the most severely ill patients”. The CGI-Improvement (CGI-I) rates the change in symptom severity and impairment from the baseline, ranging from 1 (“very much improved”) to 7 (“very much worse”). The psychometric properties of CGI have been found to be very good [5, 22]. The clinical raters assigned to each treatment condition will complete CGI-S at pre-treatment and CGI-I at post-treatment and 6-month follow-up assessment. Patients rated 1 or 2 (markedly or moderately improved from baseline) will be classified as responders, and those rated 3 or higher will be classified as non-responders.

The secondary outcome measures will be changes in the clinician-rated Liebowitz Social Anxiety Scale (LSAS) [23] and the patient-rated Social Phobia Inventory (SPIN) [24] from baseline to post-treatment. The LSAS assesses fear in and avoidance of 24 social situations in the last week, rated on 4-point scales ranging from 0 (non and never) to 4 (severe and usually) of. In the current study we will use the total score by summing both subscales. The SPIN consists of 17 items evaluating fear, avoidance, and physiological discomfort in the last week on a 5-point rating scale, ranging from 0 (not at all) to 4 (extremely). The total score is obtained by adding up the answers of the individual items.

Changes in insight in SAD-related beliefs from baseline to post-treatment and follow-up assessment will be assessed using the German version of the clinician-administered Brown Assessment of Beliefs Scale (BABS) [25–27]. The scale consists of seven items rating the degree of conviction and insight of beliefs from 0 to 4. The outcome measure will be the total score of the first six items.

In addition, symptoms of depression will be assessed by independent ratings conducted according to the German version of the Quick Inventory of Depressive Symptomatology (QIDS; 16-item version) [28] and the Beck Depression Inventory (BDI-II) [29]. For both inventories we will use total score to examine changes from baseline to post-treatment and to follow-up assessment.

Each outcome measure will be completed at the pre-treatment, at post-treatment and 6-month follow-up.

Clinical ratings are administered by independent raters blinded to condition. Raters will be trained to perform CGI, LSAS, QIDS, and BABS assessments. The interviews will be videotaped to review and assess inter-rater reliability between independent raters.

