## Methods/Design

### Design and Sample Size

The design of the study is a between group design with two treatment groups (CT plus enhanced BEs, standard CT). Patients will be randomly allocated to one of the two groups. The outcome criteria will be assessed by blinded independent raters at pre-treatment, post-treatment, and at follow-up 6months after post-treatment and treatment termination (Fig. 1).

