### Study Procedures

All subjects contacted for the study will be screened over the telephone by trained master’s level research assistants. Those who seem eligible will be invited for two in-person assessments. The screening visit will include a diagnostic interview for Axis I and II disorders (SCID-I and SCID-II) and a semi-structured interview to assess the subject’s SAD and depression symptoms and insight into SAD-related beliefs (LSAS, SPIN, QIDS, BAPS). The diagnostic interviews will be conducted by trained [doctoral-level] independent raters who are blind to treatment conditions. Patients who are eligible will be randomized either to the CT plus enhanced BEs group or to the Standard CT group and invited for a baseline visit to complete a self-reported questionnaire. The outcome measures will be assessed by the independent raters upon the termination of treatment and after 6months. The study protocol adheres to the Standard Protocol Items: Recommendations for Interventional Trials (SPIRIT) checklist (Additional file 1).

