**Data monitoring and quality assurance**

There will be no auditing process by an institution or agency independent from the investigators. The integrity of data quality is ensured by independent clinical raters assessing inclusion criteria and primary outcome. Random allocation to treatment will be administered by a psychologist from another department of the university. Adherence to trial interventions is ensured by checklists of interventions endorsed by therapists after each session, as well as videotapes of session. Supervision of therapists is provided separately by either the senior investigator for the experimental condition, or by an independent supervisor for the control condition. Allegiance of therapists in both study conditions is assessed after the pilot therapy. Completeness, accuracy, and timeliness of data collection is checked by the Co-investigators. Serious adverse events and harms are reported to the senior investigator, who will conduct interviews and refer the patient to crisis intervention in the center for psychotherapy affiliated to the department of psychology.

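### One sentence ties the raters of the primary outcome to a treatment condition, against the blinded independent rating stated elsewhere, and nothing says that raters cover both arms

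*Protocol article*

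**What the plan says.** The sentence at issue is in Outcome Measures, in the paragraph that defines the primary outcome: "The clinical raters assigned to each treatment condition will complete CGI-S at pre-treatment and CGI-I at post-treatment and 6-month follow-up assessment". (The abstract names the LSAS as primary. That is a separate matter; Outcome Measures and Analysis of Outcome Variables both name CGI-I response, and I follow them here.)

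Other sections describe the raters differently:

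- Design and Sample Size: "The outcome criteria will be assessed by blinded independent raters at pre-treatment, post-treatment, and at follow-up".
- Study Procedures, on the interviews: "The diagnostic interviews will be conducted by trained [doctoral-level] independent raters who are blind to treatment conditions"; and on later assessments: "The outcome measures will be assessed by the independent raters upon the termination of treatment and after 6months".
- The end of Outcome Measures: "Clinical ratings are administered by independent raters blinded to condition". The next sentence shows that this includes the CGI: "Raters will be trained to perform CGI, LSAS, QIDS, and BABS assessments".
- Data monitoring and quality assurance makes the raters the main safeguard: "The integrity of data quality is ensured by independent clinical raters assessing inclusion criteria and primary outcome".

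Statistical Analyses plans a chi-square or Fisher's exact test of CGI-I response with no adjustment. It provides for a therapist random term if a preliminary test points to therapist differences, but for no rater term.

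**The concern.** The CGI-I is a single global judgement by a clinician, and response turns on whether the rating is 2 or 3. Such a rating depends on where each rater sets the threshold. If every rater sees patients of both arms, differences in threshold add noise but do not favour either treatment. If each arm has its own raters, the average threshold difference between the two sets goes straight into the treatment comparison.

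Blinding would also be more fragile. In any design, a patient who talks about the therapy can unblind the rater for that patient. When a rater serves one arm only, the same remark can reveal the arm of every other patient whom that rater sees.

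The article plans no data monitoring committee and no independent audit. The integrity of the primary outcome therefore rests largely on how the raters are assigned.

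**Working it through.** No figure in the article is at stake, so the main check compares the statements.

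| Section | Time points covered | Blinded? | How raters are matched to patients |
|---|---|---|---|
| Outcome Measures, CGI paragraph | pre, post, 6 months | not stated | by treatment condition |
| Outcome Measures, end | clinical ratings in general, CGI included | yes | not stated |
| Design and Sample Size | pre, post, 6 months | yes | not stated |
| Study Procedures | diagnostic interviews; then end of treatment and 6 months | yes for the interviews; the later raters are called the independent raters | not stated |
| Data monitoring and quality assurance | inclusion criteria and primary outcome | independent; blinding not mentioned | not stated |

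Two things follow. First, the CGI paragraph is the only place that says how raters are matched to patients, and it matches them by arm. Secondly, the blinding statements do not settle that question: a rater could be kept unaware of the arm and still see only one arm's patients.

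**Illustration of size (assumed inputs).** Suppose the true response is 50% in both arms and improvement is normal on a latent scale. If the raters of one arm are more lenient by s standard deviations, and those of the other arm are not, the rated response in the lenient arm is Φ(s). The values of s are assumptions; the documents give no basis for them.

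- s = 0.10: Φ(0.10) = 0.540, a spurious difference of 4.0 points.
- s = 0.25: Φ(0.25) = 0.599, a spurious difference of 9.9 points.
- s = 0.40: Φ(0.40) = 0.655, a spurious difference of 15.5 points.

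For scale, Design and Sample Size uses d = 0.60. The article states no target difference in response. On the same latent scale, d = 0.60 gives Φ(0.60) − 0.50 = 0.226, or 22.6 points. Other conversions give 23.6 points (symmetric about 50%) and 24.8 points (logistic). Against 22.6 points, the spurious differences are 4.0/22.6 = 18% and 15.5/22.6 = 69% of the effect sought.

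**False-positive rate.** Inputs: 30 per arm and two-sided alpha 0.05 (Design and Sample Size), no treatment effect, and a rated-response difference δ placed symmetrically about 50%. Exact enumeration of the Pearson chi-square test without continuity correction (reject when |z| > 1.96) gives:

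- δ = 0: 5.2%
- δ = 10 points: 12.4%
- δ = 15 points: 21.9%

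Centring on 40% or 60% gives 4.9%, 12.2% and 21.7%.

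**The case against.** The strongest reply is that the intention is plain. Blinded or independent rating is stated in several places, once in the same section and with the CGI named. Against this stands one phrase, which might mean only that raters are provided for both conditions. This has force. A reader might infer that the trial really uses separate, unblinded raters for each arm, and the documents do not support that. The sentence does not say that raters see only one arm or that they know it. What stands is that no section says raters cover both arms, so the contradiction cannot be resolved from the text.

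Three further inferences are tempting and should not be drawn.

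- *No analysis could separate rater from treatment.* Outcome Measures has the interviews videotaped so that agreement between raters can be examined. If raters of one arm re-rated tapes of the other, a threshold difference could be estimated. The article plans this as a reliability check, not as a correction, and does not say how many tapes are rated twice. The statement therefore holds for the planned test, not for every possible analysis.
- *The rule cannot be followed at pre-treatment because screening precedes randomization.* Study Procedures does not list the CGI-S among the screening measures, and the schedule figure is not available. When the CGI-S is rated relative to randomization is unknown.
- *The bias is shown to exist.* The leniency values are assumed. The number of raters is not given, and averaging over several raters per arm would tend to shrink the difference.

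**Conclusion.** The point holds as a contradiction on the primary outcome that must be reconciled. Read as written, Outcome Measures assigns CGI raters by arm. Three sections, Outcome Measures among them, describe raters blinded to condition, and none says that raters are shared between arms.

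The consequence is conditional. If the sentence is followed literally, rater and arm are confounded, one disclosure can unblind a rater for all of that rater's patients, and the planned unadjusted test cannot separate leniency from treatment effect. Under an assumed leniency difference of 0.1 to 0.4 SD, a true 50% response in one arm would be rated as about 54% to 66%. With a 10-point rated difference and no treatment effect, the chi-square test would reject about 12% of the time instead of 5%. If the sentence is a slip and raters are shared between arms, none of this arises and only the wording is wrong. The documents do not show which of the two applies.

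**What to change.** In the CGI paragraph of Outcome Measures, delete the words that tie the raters to a treatment condition. State instead that one common pool of independent raters, blinded to condition, assesses patients of both conditions at pre-treatment, post-treatment and 6-month follow-up, and that raters are matched to patients independently of allocation.

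Matching could follow a sequence or an availability rota drawn up by someone without access to the allocation. That rules out the psychologist who administers the schedule. According to Randomization, that person knows the allocation and takes no further part in the study. It also rules out the investigators and therapists, who are told the allocation.

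The cost is one reworded sentence and a simple rota. The sample size, visits and measures do not change. The number of raters is not stated, so whether the present raters suffice is for the trial team to confirm.

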### Additional Assessments

For competence and adherence ratings, three videotapes will be selected: one from the initial stage (session 1, deriving the model) and two from the second stage (random selection from session 5–12). Session 1 is selected to cover general competencies such as guided discovery, whereas sessions from the second stage of treatment onwards are expected to refer to specific competencies (conducting BEs vs. cognitive restructuring). Competence and adherence will be rated by two independent, masked, and trained raters using the Cognitive Therapy Adherence Scale for Social Phobia (CTAS-SP) [18] the Cognitive Therapy Competence Scale for Social Phobia (CTCS-SP) [30]. The CTAS-SP comprises 17 items related to the specific interventions of CT, as described in the manual by Stangier et al. [17]. In the SOPHONET trial [6], a good interrater reliability (ICC = 0.87) was observed. Retest reliability was rtt = 0.90 for the total score and rtt = 0.28–1.0 for the individual items. Internal consistency was high (α = 0.99). Similarly, the psychometric properties of the 16-item CTCS-SP were good, with an interrater reliability of ICC = 0.81, retest reliability of rtt = 0.92, and an internal consistency of α = 0.97.

To assess the therapeutic relationship, the Helping Alliance Questionnaire (HAQ, patient and therapist version) will be used [31]. Both questionnaires will be administered at pre-treatment. The mean scores of the therapist and patient versions will be used to predict the outcomes.

Allegiance is assessed after the training and one pilot-therapy by the therapist version of the Reaction to Treatment Questionnaire developed by Holt & Heimberg [32]. For the purpose of the present study, two further items have been added to the scale referring to outcome expectations about specific intervention (BEs and cognitive restructuring).

As a predictor of treatment success, a 12-item version of the learning style inventory (Kolb LSI) will be administered at pre-treatment [33]. Based on previous treatment study results [34], it is hypothesized that the outcome of participants in the BE intervention will significantly predict an active experimentation learning style, whereas for participants in the standard CT (cognitive restructuring), the preferred learning style is predicted to be an abstract conceptualization learning style.

The SCQ (Social Cognition Questionnaire) [35] (German translation [36]) is a self-report measure to assess the frequency and intensity of SAD-related cognitions. The questionnaire will be completed by the patients at every session.

Detailed procedure of the measurements is listed in the schedule of enrolment, interventions and assessments (Fig. 2).

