### Treatments

In the study, two conditions, CT plus enhanced BEs vs. standard CT, are compared; these use different interventions in the middle stage of treatment to achieve a change in SAD-related cognitions:
behavioral experimentstraditional (verbal) methods of cognitive restructuring.

CT based upon the Clark & Wells model pursues two primary goals:
to reverse the processes that maintain SAD (self-focused attention, distorted images of the social self, and safety behaviors), andto disconfirm dysfunctional beliefs (using BE, imagery rescripting, and cognitive restructuring).

As described in detail in the revised manual [16], the treatment comprises the following interventions:
Stage 1 (sessions 1–3): deriving an individual cognitive model, experiential exercises to avoid self-focused attention and safety behaviors, providing video feedback, and enhancing attention training;Stage 2 (sessions 4–13): BEs (in-session and homework) to test dysfunctional beliefs, and imagery rescripting to modify maladaptive beliefs linked to recurrent negative imagery;Stage 3 (14–17): termination of treatment (blueprint of techniques helpful for relapse prevention) and booster session.

To implement BEs, prolonged sessions are required to prepare the experiment, including defining the expectations to be tested, outlining the behaviors to be enacted in the experiment, and choosing an appropriate situation outside the therapy room. Thus, 2 × 50 min will be scheduled as the standard duration of the session.

Furthermore, guided discovery and standard CT discussion techniques are used in stage 2 to support the reflection of BEs consequences. However, no automatic thoughts records are used, and verbal techniques of cognitive restructuring are embedded in the planning of BEs and the analysis of the results. In contrast to standard CT, therapists will use the Social Cognitions Questionnaire (SCQ) on a weekly basis to determine the focus of the therapy.

As in standard CT, neither exposure based on a rational habituation nor formal social skills training is used.

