Standard CT comprises similar elements in the first and third stage of therapy; however, in the middle stage (stage 2), discussion techniques of challenging dysfunctional beliefs are used instead of BE. The techniques are described in detail in the previous manual [17] and include Socratic dialogue, the downward arrow technique, the prejudice technique, the life chart technique, positive data log, automatic thoughts protocol, and the pie chart technique. Dysfunctional beliefs associated with early experiences are identified and discussed. Homework mainly focuses on automatic thoughts and the practice of Socratic dialogue.

In standard CT, therapists are not encouraged to use BEs. Neither exposure based on a habituation rational nor formal social skills training is used.

To equalize therapists’ contact time and treatment dose, both treatments comprise the same amount of contact hours. In line with short-time-therapy in Germany, 25 units of 50-min duration are provided. In CT + BEs, up to eight sessions last 100 min due to the implementation of BEs. Standard CT includes one session of 100-min duration. Thus, the total number of sessions differs (17 vs. 25). The length of both treatments, however, is 6 months, since booster sessions are conducted (4-week interval) in the end of CT + BEs as prescribed in the manual.

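### The videotape window for stage 2 fits the 17-session arm only, so independent ratings cover the two arms' middle stages unequally

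*Protocol article*

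**What the plan says.** Additional Assessments (protocol article) selects three tapes, the two middle-stage ones by session number: "one from the initial stage (session 1, deriving the model) and two from the second stage (random selection from session 5–12"). It gives no separate range for either arm. It plainly means both, because the ratings are "expected to refer to specific competencies (conducting BEs vs. cognitive restructuring").

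Adherence Checks describes the selection differently: "three randomly selected videotapes of each treatment (one from stage 1 and two from stage 2) will be rated". That rule goes by stage and has no session window. It also makes all three tapes random, whereas Additional Assessments fixes the first one at session 1.

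Session numbers for stages appear only under Treatments, in the description of the revised manual:
- "Stage 1 (sessions 1–3): deriving an individual cognitive model"
- "Stage 2 (sessions 4–13): BEs (in-session and homework) to test dysfunctional beliefs"
- "Stage 3 (14–17): termination of treatment"

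These add up to 17 sessions. For standard CT, the same section says that the first and third stages have similar elements and that the middle stage uses discussion techniques in place of BEs. It numbers none of that arm's stages. On length it says: "Thus, the total number of sessions differs (17 vs. 25").

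Adherence Checks also has therapists fill in a checklist of the interventions used after every session, in both arms.

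**The concern.** Sessions 5–12 are stage 2 of the 17-session schedule without its first and last session. In a 25-session treatment with similar opening and closing stages, stage 2 should run well past session 13, so the same window reaches only its earlier part.

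Three uses of the ratings depend on this. Hypothesis 2 compares BE-related adherence between arms. Hypothesis 4 and the predictor analysis (Statistical Analyses) use adherence and competence as predictors of response, with treatment interactions. The tapes are also the only masked evidence that standard CT therapists, who are not encouraged to use BEs, kept to their own techniques. If ratings change over the course of stage 2, a difference between arms in the ratings is partly a difference in when the tapes were taken.

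**Working it through.** **Inputs.** The window is sessions 5–12, which is 8 sessions, of which 2 are drawn (Additional Assessments). In CT plus BEs, stage 1 is sessions 1–3, stage 2 is 4–13 and stage 3 is 14–17 (Treatments). Each arm has 25 units of 50 minutes, with up to eight double sessions in CT plus BEs and one in standard CT (Treatments).

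**Step 1: reproduce the session counts.** Sessions = doubles + (25 − 2 × doubles).
- CT plus BEs: 8 + (25 − 16) = 17, as stated.
- Standard CT: 1 + (25 − 2) = 24, against the stated 25. Twenty-five sessions with one double would need 26 units. Both totals are carried forward.

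**Step 2: coverage in CT plus BEs.** Stage 2 has 10 sessions and 8 lie in the window. Eligible: 8/10 = 80%. Not eligible: 20%.

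**Step 3: coverage in standard CT.** The boundaries are not given, so this step rests on an assumption. With stage 1 = a sessions, stage 3 = c sessions and T in total, stage 2 runs from session a + 1 to session T − c.

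| T | a | c | Stage 2 | In window | Not eligible |
|---|---|---|---|---|---|
| 25 | 3 | 4 | 4–21 (18) | 8 | 10/18 = 56% |
| 24 | 3 | 4 | 4–20 (17) | 8 | 9/17 = 53% |
| 25 | 5 | 4 | 6–21 (16) | 7 | 9/16 = 56% |
| 25 | 4 | 5 | 5–20 (16) | 8 | 8/16 = 50% |
| 24 | 4 | 6 | 5–18 (14) | 8 | 6/14 = 43% |

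The first two rows keep the stage lengths of CT plus BEs. Over all combinations of a = 3–5, c = 4–6 and T = 24 or 25, the part not eligible runs from 43% to 56%. With a = 5, session 5 of the window would itself belong to stage 1.

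**Step 4: the case in which the window would be even.** If stage 2 of standard CT also ended at session 13, coverage would be 80% there too. Stage 3 would then take 25 − 13 = 12 sessions (11 of 24), against 4 in CT plus BEs. That does not sit well with a closing stage of similar content.

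**Step 5: contact time at session 12.** Suppose all eight doubles take place and all fall in stage 2. Then 7 or 8 of them are over by session 12, and CT plus BEs has delivered 12 + 7 = 19 or 12 + 8 = 20 of 25 units (76–80%). Standard CT has delivered 12 or 13 of 25–26 units, which is between 12/26 = 46% and 13/25 = 52%. Equal session numbers are therefore not equal points in treatment.

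**The case against.** A reader might infer that half of standard CT's middle stage is never checked for adherence or contamination. The documents do not support that. The checklist covers every session, and Adherence Checks defines adherence to include avoiding proscribed interventions, so a BE in a late control session can be recorded. The section on data monitoring and quality assurance repeats that checklists and tapes are used together, and gives the control arm its own independent supervisor. What is lost is independent rating. The checklist is unmasked self-report by the therapists being assessed, and it records which interventions were given, not how well. Competence has no source other than the tapes.

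Other limits also stand. Hypothesis 2 covers BE-related adherence and allegiance, not competence; competence enters through the secondary objective and Hypothesis 4. The control-arm percentages depend on stage lengths that the article does not give. That the window was derived from the 17-session schedule is an inference, though the numbers match. Late drift to BEs is a plausible risk that nothing in the documents demonstrates. Each arm still yields two stage 2 tapes per treatment, so the problem is what the tapes represent, not how many there are.

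The remaining defence is that equal session numbers match the two arms on exposure. It fails: the protocol gives no such reason, both descriptions frame the sampling by stage, and session length differs between arms (step 5).

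**Conclusion.** The point holds for independent video rating. Followed as written, the plan makes 80% of stage 2 eligible in CT plus BEs. In standard CT it makes about 44–57% eligible, assuming 3–5 sessions in stage 1, 4–6 in stage 3, and 24 or 25 in total. The imbalance appears in every combination examined and would disappear only if standard CT had a much longer closing stage.

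The consequence is confined to the video-based part of Hypothesis 2, the adherence and competence predictors with their interactions under Hypothesis 4, and the masked evidence on treatment integrity. How far the ratings would shift cannot be judged from the documents, which do not say whether adherence or competence changes during stage 2. The primary CGI-I comparison is untouched. Severity is minor. Confidence is medium, because the standard CT boundaries are not stated.

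**What to change.** 1. State the session range of each stage of standard CT, and reconcile its 25 sessions with 25 units that include one double session.
2. Define the tape window by arm: draw both stage 2 tapes at random from that arm's whole stage 2, or from the same proportion of it in both arms.
3. Bring Adherence Checks and Additional Assessments into line on whether the first tape is session 1 or a random stage 1 session, and on whether stage 2 is sampled whole or within a window.

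Drawing one tape from each half of stage 2 would spread the ratings further, but is optional. The cost is a few sentences in Treatments, Adherence Checks and Additional Assessments. The number of tapes and raters does not change. If tapes have already been selected under the present window, report the session number of each rated tape by arm and state the limitation.
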